#### ii) **Stress, anxiety, depression and personally identified problems**

We will use Generalized Anxiety Disorder 7-item (GAD-7) for anxiety assessment, Patient Health Questionnaire-9 (PHQ-9) for depression and Perceived Stress Scale (PSS-9) for stress. In a study among adolescents and young people (AYP) in Nairobi and Kiambu counties in Kenya, both the PHQ-8 ( $\alpha = 0.78$ ) and GAD-7 ( $\alpha = 0.82$ ) showed good internal consistency and goodness of fit (Osborn et al., 2021).

The GAD-7 has been used and has met psychometric standards in prior studies with Kenyan adolescents (Osborn et al., 2020; Osborn et al., 2021). Cronbach  $\alpha$  was 0.82 in a Kenyan adolescent sample (Osborn et al., 2020).

We will assess personally identified problems using the Psychological Outcome Profile (PSYCHLOPS), a sensitive measure of change in participants' identified problems after intervention with high internal reliability (Ashworth et al., 2009).

The secondary outcome will be the effectiveness of the intervention in improving functioning and resilience and will involve the following outcome measures.

#### i) **Functioning**

The functioning of the participants will be assessed using the WHO Disability Assessment Schedule (WHODAS 2.0) tool, developed by WHO to assess health and disability. It has six domains: mobility, self-care, life activities, getting along, cognition and participation. The 12-item version will be used in this study (WHO, 2016). The WHODAS 2.0 measures activity function and participation in daily activities in the 30 days preceding its application (WHO, 2010; Üstün et al., 2010). The assessment will be done pre- and post-intervention.

#### ii) **Resilience -measured using the Brief Resilience Scale**

The participants' level of resilience will be assessed using the Brief Resilience Scale (Smith et al., 2008).

### Data collection process

### Quantitative data collection

The data will be collected by trained research assistants who administer the questionnaire face-to-face. Each interview will last approximately 30 minutes. KoboTool box will be used for data collection using tablets, and no physical papers will be used during the process.

A questionnaire assessing participants' demographic information, including age, gender, area of residence, the highest level of education, and work status, will be administered at pre-test followed by the outcome measure questionnaires: PHQ-9 for depression, GAD-7 for anxiety, PSS-10 for stress, PSYCHLOPS for self-identified problems, BRS for resilience, and WHODAS for functioning and knowledge and attitude on mental health questionnaire.

### Data analysis

The collected quantitative data in the Kobotool box will be imported into the Statistical Package for Social Sciences (SPSS) Version 27.0, where it will be coded and ready for analysis. Both per protocol and Intention to treat analysis (ITT) will be used in the analysis.

For descriptive analysis, mean and standard deviation or median and corresponding interquartile range will be used for continuous variables such as age, scores on depression, anxiety, stress, WHODAS, and BRS scales. For categorical variables such as gender and level of education, frequencies and percentages will be used to describe them.

To compare baseline characteristics between the intervention and control groups,  $\chi^2$  tests for comparison of frequencies and independent-sample t-tests for comparison of mean scores on normally distributed continuous measures or the Mann-Whitney U-test for comparison of the median for skewed continuous variables will be used.

The possible impact of missing data will be examined via sensitivity analyses of augmented data sets, and missing data will be handled through modern imputation techniques such as multiple imputation.

A mixed-effect linear model will be used to determine the effectiveness of the intervention, controlling for participants' sociodemographic characteristics found to be significantly different between the two groups, and the pre-assessment outcome scores.

The significance level based on a two-sided will be taken as  $P < 0.05$  at 95% confidence intervals.

For mental health outcome measures, we will also use the Reliable Change Index (RCI) and Clinically Significant Change (CSC) approaches, classifying participants as 'recovered' or 'improved', 'unchanged' and 'deteriorated' for each outcome (Jacobson & Truax, 1991). These approaches comprise measures of whether the change in scores is larger than expected due to outcome measure reliability and whether participants shift from clinical to non-clinical.

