#### Randomization

Cluster randomization will be used with the cluster defined as barbers/barbershops, and all participants recruited and offered intervention by each barber randomized to the same group as the barber (either intervention or control group). Randomization at the level of individual youth will not be feasible owing to the danger of contamination.

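### Sociodemographic covariates for the effectiveness model are chosen by baseline significance tests that ignore clustering, so the model is not fixed in advance and loses precision

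*Protocol*

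**What the plan says.** The Data analysis section gives one regression model for effectiveness: "A mixed-effect linear model will be used to determine the effectiveness of the intervention". It adjusts for "sociodemographic characteristics found to be significantly different between the two groups, and the pre-assessment outcome scores". The pre-assessment score is thus always in the model, whereas a sociodemographic variable enters only if it differs significantly between arms.

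The same section describes the between-arm baseline tests. They are introduced with "To compare baseline characteristics between the intervention and control groups" and consist of chi-square tests and "independent-sample t-tests for comparison of mean scores on normally distributed continuous measures or the Mann-Whitney U-test". The threshold is P < 0.05, two-sided. No adjustment for clustering is stated for these tests.

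The Randomization section makes the shop the unit: "Cluster randomization will be used with the cluster defined as barbers/barbershops". The Allocation section puts 20 clusters of 15 youths in each arm by simple randomisation, with no stratification stated. The Target population section places 20 barbershops in each county. The Quantitative data collection section names five candidate variables: "age, gender, area of residence, the highest level of education, and work status".

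**The concern.** There are two separate faults.

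- **The criterion is the wrong one.** Adjustment improves an estimate to the extent that a covariate predicts the outcome. A between-arm p-value at baseline does not measure that. A strong predictor that happens to be balanced is left out, while a weak one that happens to be imbalanced enters.
- **The tests that apply the criterion do not match the design.** Chi-square, t and Mann-Whitney tests on individual youths treat 600 observations as independent, although 40 shops were allocated. They flag chance differences more often than the nominal 5%.

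What is at stake is precision and a model specified in advance. Nobody can write down the effectiveness model until the baseline data have been tested. The protocol also plans both intention-to-treat and per-protocol analyses. If the rule were applied afresh in each set (the protocol does not say), the two could use different covariates, and a change of population would be mixed with a change of model.

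**Working it through.** The protocol gives no figure for how this selection rule behaves, so there is nothing of its own to reproduce first.

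**Inputs from the protocol.** 40 shops, 20 per arm, 15 youths each (40 × 15 = 600; 300 per arm); ICC 0.02, given for the outcome in the Sample size section; two-sided 0.05; five named sociodemographic variables; 20 shops per county.

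**Inputs that are assumptions.** Any ICC for a baseline covariate, independence of the five variables, how area of residence is recorded, and how strongly the covariates predict outcome. The protocol gives none of these.

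**1. Rejection rate of an individual-level baseline test.**
- Design effect = 1 + (15 − 1) × 0.02 = 1.28.
- Actual rate = 2 × (1 − Φ(1.96/√1.28)) = 2 × (1 − Φ(1.732)) = 8.3%.
- For assumed covariate ICCs of 0.01, 0.05 and 0.10 the same formula gives 6.6%, 13.3% and 20.6%.

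**2. Chance that at least one of five independent variables is flagged.**
- Valid 5% tests: 1 − 0.95⁵ = 23%.
- ICC 0.02: 1 − (1 − 0.0832)⁵ = 35%.
- Assumed ICC 0.10: 1 − (1 − 0.2058)⁵ = 68%.

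Most of the 35% therefore comes from testing five variables at all. Ignoring clustering adds about 12 percentage points at the protocol's own ICC.

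**3. County, if area of residence is recorded as county.**
- Suppose 11 of one county's 20 shops fall in one arm and 9 in the other. The youth-level comparison is 165/300 v 135/300, a difference of 0.10 with variance 0.25 × (2/300). Chi-square = 0.01/0.001667 = 6.0, p = 0.014.
- Counted by shop, the same split is 11/20 v 9/20: chi-square = 0.01/(0.25 × 2/20) = 0.4, p = 0.53. This is an ordinary result of allocation.
- The chance of an exact 10:10 split under unstratified 20:20 allocation is C(20,10)²/C(40,20) = 184,756²/137,846,528,820 = 0.248. Every other split is at least as uneven as 11:9, so about 75% of allocations would flag county.

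**4. Effect on the treatment comparison.** A null simulation used 4,000 trials per setting, with 20 shops of 15 per arm and no dropout. Outcome ICC was 0.02, baseline correlation 0.5, covariate ICC 0.02 or 0.10, and the treatment test allowed for clustering. Covariate effects are per SD of the covariate, in units of the outcome SD before the covariates' contribution is added.

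| Covariate ICC | Effect of each of five covariates | SD of estimate: protocol's rule | SD of estimate: all five fixed | Type I error: rule | Type I error: fixed |
|---|---|---|---|---|---|
| 0.02 | 0 | 0.080 | 0.080 | 4.4% | 4.6% |
| 0.02 | 0.15 | 0.085 | 0.081 | 4.5% | 5.1% |
| 0.02 | 0.30 | 0.095 | 0.082 | 3.9% | 5.3% |
| 0.10 | 0 | 0.081 | 0.081 | 4.8% | 4.7% |
| 0.10 | 0.15 | 0.084 | 0.081 | 3.8% | 5.1% |
| 0.10 | 0.30 | 0.095 | 0.080 | 2.6% | 4.6% |

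At 0.30 the variance ratio is (0.0954/0.0822)² = 1.35 to (0.0949/0.0800)² = 1.41, so the rule costs about 35–40% in variance. That is a strong assumption: the five covariates then explain 5 × 0.09 = 0.45 of a total 1.45, or 31% of outcome variance. At 0.15 they explain 0.1125/1.1125 = 10%, and the cost is (0.0848/0.0814)² = 1.09 or (0.0835/0.0808)² = 1.07. With no prognostic value there is no cost.

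**The case against.** A fair defence has several parts.

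- **The treatment test is not inflated.** A reader might infer from tests that ignore clustering that the trial's false-positive rate is raised. The documents do not support this: the effect comes from a mixed model, and selection uses baseline data only and never sees outcomes. In simulation the test ran at 2.6–4.8%. This stands.
- **Power is ample.** With the protocol's inputs and 12 completers per shop, power for d = 0.40 is 97–99%. Even at the larger SD, 0.40/0.095 is about 4.2 standard errors. The main conclusion is unlikely to change, which limits the severity.
- **The larger rates are not the protocol's.** A reader might infer that the baseline tests reject far too often. At ICC 0.02 it is 8.3% against 5%; the 13% and 21% figures need covariate ICCs that the documents do not give.
- **Area of residence is undefined.** A reader might take it as fixed by shop. It could be neighbourhood or another unit, so the 75% figure is conditional. Where it applies, the rule would usually adjust for county, which is sensible in itself. The fault is that adjustment depends on the allocation.
- **Looking at baseline differences has a use here.** Unblinded barbers approach the youths, and the protocol does not state that recruitment precedes allocation, so differences may reflect recruitment rather than chance. This is a reason to examine balance with suitable methods. It does not justify letting the result choose the covariates.
- **The protocol does not tie these tests to the selection step in so many words.** True, but it describes no others. An unseen analysis plan does not answer the point either, because the protocol itself states the rule.

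**Conclusion.** The point holds and should be fixed, but it does not threaten the validity of the treatment test. The protocol fixes a poor selection rule for the sociodemographic part of its only effectiveness model. The baseline outcome score is outside the rule.

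That the criterion is wrong and the model is unknown in advance follows from the text and needs no assumption. The 8.3% carries the outcome ICC over to the covariates. The 35% (against 23% with valid tests) also treats the five variables as independent. The county result rests on residence being recorded as county. The precision loss, SD 0.095 against about 0.081, rests on all five covariates being prognostic at 0.3 SD each; it shrinks to little or nothing if they are weak.

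**What to change.** Before unblinded data are seen, replace the selection rule with one covariate set, used for every outcome whatever imbalance is observed:

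- the baseline score of that outcome;
- named sociodemographic variables already collected, for example age, gender, education and work status;
- county, which is known from the shop;
- barber/barbershop as a random intercept.

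State that the same set applies to the intention-to-treat and per-protocol analyses. Present baseline characteristics descriptively by arm. If baseline differences are examined to detect differential recruitment, use methods that account for clustering, and state that the result does not decide the covariates.

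The cost is one paragraph of wording and no new data. The model gains a few parameters, which is small for 600 youths in 40 clusters. County is the only addition at shop level and takes one degree of freedom there (40 − 2 = 38 becomes 37).

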### **Qualitative data collection and analysis**

A purposive sample of 12 participants will be used (8 youths involved in the intervention and four barbers engaged in its delivery). However, the sample will be increased or reduced based on the attainment of conceptual saturation when no new information is forthcoming.

In-depth interviews will be conducted with barbers and project participants (youths). Two different pre-prepared interview guides for youths and barbers will be used during the interview process. The guides contain open-ended questions. For barbers, the interview will seek to determine their experience delivering the intervention, the challenges encountered, and how it can be improved in the future. The interview guide for the youths will contain open-ended questions on their views on mental health-themed music, any role it played in their participation in the project, what they learned from the music, their experiences and engagement with the intervention, satisfaction, challenges faced, and any improvements needed.

A trained research assistant, competent in in-depth interviewing and qualitative research, will conduct the interviews. The interviews will be conducted either in Swahili or English based on the participants' preferences and capabilities. The interviews will be tape-recorded with the participant's consent.

The qualitative data will be transcribed verbatim before analysis using thematic analysis, which involves identification, analysis, and reporting patterns within data, resulting in the minimal organisation and minimal description of the data in rich detail (Braun and Clarke, 2006), will be used. In the process, an inductive approach will be taken, where the analysis

is data-driven without trying to fit it into any pre-existing framework (Thomas, 2006). The thematic analysis process will be based on Braun and Clarke (2006).

#### Ethical considerations

The protocol for this study will be sent to Moi University/ Moi Teaching and Referral Hospital (MTRH) Institutional Research Ethics Committee (IREC) for ethical review and approval. Permit to conduct the study in the selected regions will also be obtained from the National Commission for Science, Technology, and Innovation (NACOSTI) as local Kenyan laws require. The County Department of Health (CDOH) and the county commissioners of the study counties will be notified, and supporting letters will be obtained from their offices to help facilitate fieldwork.

#### Dissemination of findings

The study's findings will be shared with the county government of Bungoma and Trans-Nzoia health departments in the form of the final report and a short policy brief highlighting the key findings. The study results will be presented at local and international mental health conferences and published in reputable peer-reviewed journals.

## Study timelines

|                                          | Dec
2022-Jan
2023 | Feb-
May
2023 | May-
June
2023 | June
2023-
April
2024 | May-
July
2024 | Aug-
Nov
2024 |
|------------------------------------------|----------------------------------|------------------------------|-------------------------------|------------------------------------------|-------------------------------|------------------------------|
| IRB
Preparation/
Approval          |                                  |                              |                               |                                          |                               |                              |
| Fieldwork
preparation and
training |                                  |                              |                               |                                          |                               |                              |
| DWM
intervention
delivery          |                                  |                              |                               |                                          |                               |                              |
| Economic
empowerment
component     |                                  |                              |                               |                                          |                               |                              |
| Report
Preparation                    |                                  |                              |                               |                                          |                               |                              |

